### Interventions

The LNG-IUD is approved for contraception, treatment of idiopathic menorrhagia, and prevention of endometrial hyperplasia. The most common adverse reactions are uterine/vaginal bleeding alterations, amenorrhea, intermenstrual bleeding and spotting, abdominal/pelvic pain, and ovarian cysts. The device is prohibited for use in women with known or suspected pregnancy, congenital abnormal uterine development, breast cancer, unexplained vaginal bleeding, reproductive tract infection, and other conditions.

Systemic progestogen therapy, such as MA 160 mg orally once a day, is effective for the treatment of hormone-sensitive hyperplasia and tumors [32]. However, PRs are often downregulated leading to a relatively short duration of effectiveness [33]. In addition, systemic therapy is associated with low compliance rates due to adverse effects including nausea, thromboembolic complications such as deep vein thrombosis (DVT), pulmonary embolism (PE), stroke, weight gain, abnormal vaginal bleeding, and increased risk of breast cancer [34].

Study participants will be instructed to take metformin with meals, 1000 mg daily. This dose is similar to that used in clinical trials as an adjuvant breast cancer treatment (NCT00909506 and NCT01302002), ranging from 500 to 1000 mg daily. Metformin is well-tolerated by the vast majority of patients with no significant side effects. The gastrointestinal adverse effects of metformin are dose-dependent [35]. The dose of 1000 mg daily can be reduced to 500 mg daily if needed. Metformin is associated with abdominal pain, diarrhea, lactic acidosis, nausea and vomiting, and taste changes [35]. Metformin decreases absorption of vitamins B9 and B12, in turn elevating homocysteine levels. Metformin is not used for patients with moderate or worse renal function impairment.

Because all participants in the trial will be obese, a weight loss program will be implemented. The weight loss program is an evidence-based and tested diet and exercise intervention program that has led to weight loss success in obses people [36]. Exercise levels (sedentary, moderately active, and sufficiently active) will be measured using the Active Australia Survey [37].

### Randomization

Patients will be randomly assigned to arm A (LNG-IUD plus metformin) or arm B (MA plus metformin) in a 1:1 ratio by an internet-based distant third-party statistician blinded to the study and participant details. The doctor involved in recruitment will receive training and instructions on the recruitment procedure.

### Treatment of adverse events

Any adverse events will be managed by local investigators according to current good clinical practice guidelines. The details of each adverse event will be described in a case report form, including the nature of the adverse event, time of onset and time of resolution, severity, treatment, and outcome. If necessary, a followed-up examination will be performed to ensure patient safety.

If the physician monitoring the trial finds evidence of harm to a participant or signs of ineffectiveness, the participant will be withdrawn from the study. The results of these participants will be analyzed as a non-pCR group.

### Criteria for discontinuation of trial treatment

The criteria for the discontinuation of a trial medication are as follows:A participant declines further participation or withdraws their consent.Cancelation of the entire study.The protocol treatment will be stopped if it does not result in remission according to the following criteria: no treatment response or pCR by 1 year; disease progression at any time; relapse after remission.Severe adverse events (progressive or persistent) which may be related to the medication (such as hemorrhagic shock due to massive vaginal bleeding, severe allergy, thrombosis, liver function damage) and newly diagnosed other malignancy (e.g., breast cancer) will be evaluated by 2 chief physicians before the trial is stopped.Any situation in which the LNG-IUD, MA, or metformin treatment cannot be continued according to the judgment of the physician.

### Discontinuation of the study

The study will be terminated early if the IRB determines the occurrence of any of the following: serious adverse drug effects (abnormal liver function unresponsive to treatment, thrombus, hemorrhagic shock due to massive bleeding, severe allergic reaction); other newly diagnosed malignancy; the participants with unexpected, significant or unacceptable risks (such as death); the trial treatment is determined to be ineffective.

### Baseline assessments

Baseline assessments will be performed according to the trial standard operating procedure (SOP), including medical history, determination of BMI, CT and MRI imaging, blood tests including tumor marker CA125. Endometrial tissue specimens will be obtained by treating gynecologic oncologists via hysteroscopy and D&C. Histopathological examination of tissue specimens will confirm the cell type and grade of differentiation. Histopathological specimens will also be used for pathological molecular typing.

### Efficacy assessments

Assessments of effectiveness will be performed at 3, 6, 9, 12, 18, and 24 months after beginning treatment, including weight loss, histological examination of endometrial tissue specimens, and pregnancy outcomes. The total study duration will be 2 years.Weight loss of patients in the 2 groups will be evaluated.Hysteroscopic endometrial curettage will be performed to rule out disease progression (Fig. 2).Complete pathological response is defined as 2 consecutive negative endometrial biopsies. Endometrial tissue for pathological examination will be obtained during hysteroscopy. Tissue pathological examination will be performed in a double-blind manner by 2 senior pathologists. A third pathologist will be consulted if the results are inconsistent.A.If the disease progresses, such as atypical hyperplasia to endometrial cancer, well-differentiated adenocarcinoma of the endometrial to moderately or poorly differentiated endometrial cancer, or other types of endometrial cancer, hysterectomy will be recommended.B.If complete remission is achieved (2 consecutive negative endometrial biopsies), the patient will be recommended to remove the LNG-IUD or discontinue oral progesterone. Patients will continue to take metformin and monitor ovulation if pregnancy is desired. Participants who are not pregnant will be followed-up every 3 months for endometrial biopsy. Patients with a successful pregnancy and delivery who desire to retain reproductive function will undergo regular endometrial biopsies and imaging studies.C.If there is no response to treatment, but no progression or partial response, the current treatment will be continued; assessments and efficacy evaluations will be performed every 3 months. If there is progression or recurrence after remission, the patient will be recommended to terminate participation in the trial. If the assessments continue to indicate no response or partial response, assessments will be continued every 3 months for 12 months. If assessment at 12 months indicates an incomplete response, the patient will be recommended to terminate participation in the trial.D.If EC develops during follow-up after a complete response, it will be considered a recurrence and surgical treatment will be recommended.E.If there is no improvement or partial response after 12 months of treatment, the patient will be informed of the risks of continuing conservative treatment and a hysterectomy will be recommended.Pregnancy assessment: outcomes of abortion, premature delivery, and full-term delivery will be recorded.

**Fig. 2 Fig2:**
[figure not shown]
Assessment of pCR during treatment. *CR* complete response, *PR* partial response, *SD* stable disease, *PD* progressive disease. *Protocol treatment is halted

### Follow-up evaluations

At the 3-month follow-up, if endometrial pathology shows progressive disease, the patient will be withdrawn from the trial. If the endometrial pathology indicates a complete response, partial response, or stable disease, the patient will be followed-up after 3 months. At the 6 month follow-up, if the endometrial pathology shows progressive disease or recurrence, the patient will be withdrawn from the trial. If the pathology shows a complete response, partial response, or stable disease, the patient will be followed-up after 3 months. At the 9-month follow-up, if the endometrial pathology shows progressive disease or recurrence, the patient will be withdrawn from the trial. If the pathology shows a complete response, partial response, or stable disease, the patient will be followed-up after 3 months. At the 12-month follow-up, if the endometrial pathology shows a partial response, progressive disease, stable disease, or recurrence, the patient will be withdrawn from the trial. If the pathology shows a complete response, the patient will be followed-up in 6 months. At the 18-month follow-up, if the endometrial pathology shows an incomplete response, the patient will be withdrawn from the trial. If there is a complete response, the patient will be followed-up after 1 year. At the 24-month follow-up, if the endometrial pathology shows an incomplete response, the patient will be withdrawn from the trial. In the case of a complete response, the patient will continue to be followed long-term.

The study duration is 2 years, but the treatment and follow-up of patients will be long-term. A hysterectomy will be recommended for patients who have a complete response and have completed childbirth. Patients who have fertility requirements or are unwilling to undergo a hysterectomy will be followed closely for signs of recurrence.

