### Sample size

According to a previous study, the mean pCR rate for LNG-IUD alone was 68% (95% confidence interval [CI]: 45–86%) [30], it was assumed that the rate in the MA-alone group will be 60%. Based on a prior study [38], we anticipate that the true pCR rate will be closer to the lower confidence limit of 45%. Patients who become pregnant during the trial will be withdrawn from the study and treated as non-recurrence in-trial cases.

The sample size was estimated by software G*Power version 3.1 (Heinrich-Heine-Universität Düsseldorf, Düsseldorf, German). The effect size, w, of the 2-group contingency table was set at a medium level of 0.3, type I error (alpha) at 0.05, 2-tailed, and power was set at 0.80, chi-square test. The size ratio between the 2 groups was set at 1:1. The estimated minimum required sample size of each group is 44, and the total sample size is 88.

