### Statistical analysis

The EHA and EC pCR rates and 95% CIs will be calculated for both groups. Patient’s quality of life will be assessed at baseline, week 1, and at 3, 6, 9, 12, 18, and 24 months. Other data acquisition and analyses will include the complete response rate for the trial treatment period; the rate of trial continuation for the LNG-IUD plus metformin and MA plus metformin groups; BMI values and homeostatic model assessment of insulin resistance (HOMA-IR) results of all response cases that wish to become pregnant; the proportion of patients that become pregnant at least once during the trial period; pregnancy outcomes (miscarriage, stillbirth, live birth, and weeks of gestation); and the proportion of patients that give birth to a child. Data will be reported as mean and standard deviation (SD), median and interquartile range (IQR), or number and percentage (%) based on if the data are continuous or categorical and on the normality assumption. The Kolmogorov–Smirnov normality test will be used to check the normality of continuous variables. For comparisons between 2 groups, Student’s t-test or the Mann–Whitney U test will be used according to the normality assumption. The Chi-square test will be used to compare the number of cases and percentage between groups.

This study will also investigate changes in the expression of molecular biomarkers. Since the changing results over time are repeated measurements, statistical tests of dependent data, such as the paired t-test or mixed-design ANOVA will be used.

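### Three sections disagree on whether non-response ends treatment or trial participation; as written, a projected 32 to 48 of 88 women would leave by month 12 with no stated later data collection

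*Protocol article*

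**What the plan says.** Three sections of the protocol article deal with the same events: progression, relapse after remission, and lack of complete response at one year.

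- **Follow-up evaluations** makes leaving the trial automatic. Progression has this effect at month 3, and progression or recurrence at months 6 and 9. At month 12 the rule widens: "if the endometrial pathology shows a partial response, progressive disease, stable disease, or recurrence, the patient will be withdrawn from the trial". An incomplete response at month 18 or 24 has the same consequence.
- **Criteria for discontinuation of trial treatment** lists these events under the medication: "The protocol treatment will be stopped if it does not result in remission according to the following criteria".
- **Efficacy assessments**, item C, says that a woman with progression, recurrence or incomplete response at 12 months will be advised to end participation, which leaves the choice to her. Item E adds, for no improvement or partial response after 12 months, that "the patient will be informed of the risks of continuing conservative treatment and a hysterectomy will be recommended". Some women may therefore go on with conservative care.

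The outcomes that need later follow-up are also stated. The abstract and introduction put pregnancy outcomes and recurrence in the primary aim beside pCR. Statistical analysis plans "the proportion of patients that become pregnant at least once during the trial period", and the proportion who give birth. Table 1 schedules adverse events to month 24. The study lasts two years.

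**The concern.** Stopping a treatment and leaving a trial are different acts, and a mandatory exit differs from an advised one. A centre that applies Follow-up evaluations literally closes the record at progression, at recurrence, and at month 12 for every woman with partial response or stable disease. Months 18 and 24 then hold only women selected by an outcome that arises after randomisation.

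Hysterectomy is recommended for progression and for women without complete response at 12 months. Their final pathology is direct evidence on what up to a year of conservative treatment meant for non-responders, yet no section says that it will be recorded. Later adverse events, and pregnancies in women who decline surgery, are in the same position. The size of this loss depends on response, and response is what the trial compares, so the loss may differ between arms.

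**Working it through.** **Inputs.** From Sample size: "The estimated minimum required sample size of each group is 44, and the total sample size is 88"; the effect size w "was set at a medium level of 0.3, type I error (alpha) at 0.05, 2-tailed, and power was set at 0.80, chi-square test"; "the mean pCR rate for LNG-IUD alone was 68% (95% confidence interval [CI]: 45–86" (per cent); and "it was assumed that the rate in the MA-alone group will be 60" (per cent). The same section expects the true rate to lie ner the lower limit, 45%. The introduction gives 57% for LNG-IUD plus metformin in an earlier randomised trial. The Design section expects 3% progression.

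**The plan's own figure.** For a chi-square test with 1 degree of freedom, N = ((z₀.₉₇₅ + z₀.₈₀)/w)² = ((1.960 + 0.842)/0.3)² = 87.2, rounded up to 88. Power at N = 88 is 0.8035. The stated 88 reproduces, so 44 per arm is a sound base for the projection.

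**Expected women without pCR at month 12** = 44 × (1 − p_LNG) + 44 × (1 − p_MA).

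| pCR, LNG-IUD arm / MA arm | LNG-IUD arm | MA arm | Total | Share of 88 |
|---|---|---|---|---|
| 68% / 60% | 14.1 | 17.6 | 31.7 | 36% |
| 57% / 60% | 18.9 | 17.6 | 36.5 | 42% |
| 45% / 60% | 24.2 | 17.6 | 41.8 | 48% |
| 45% / 45% | 24.2 | 24.2 | 48.4 | 55% |

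The 3% progression is 88 × 0.03 = 2.6 women, already inside these totals. Women who reach pCR and relapse by month 12, and women withdrawn because of pregnancy (Sample size), are not counted. Binomial variation around an overall rate of 64% (the mean of 68% and 60%) gives 23 to 41 women; around 45% it gives 39 to 57.

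**Difference between arms.** At 68% / 60% the MA arm loses 17.6 − 14.1 = 3.5 more women. At 45% / 60% the LNG-IUD arm loses 24.2 − 17.6 = 6.6 more. The direction depends on which planning rate is right.

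**What each outcome loses under the literal rule.**

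- 12-month pCR: essentially nothing. These women are observed non-responders, and Treatment of adverse events counts those withdrawn for harm or ineffectiveness as non-pCR.
- Progression or recurrence on biopsy: recorded, because the finding is what triggers withdrawal.
- Hysterectomy pathology: after withdrawal, with no stated collection.
- Adverse events between withdrawal and month 24: no stated collection, apart from follow-up examination where needed for an event already reported.
- Pregnancy and birth: at risk mainly in women who do not have surgery. The documents give no figure for how many that is.

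**The case against.** The strongest reply is that withdrawal does not reliably mean the end of data collection in this article. Sample size withdraws women who become pregnant, yet Efficacy assessments and Statistical analysis plan to record how their pregnancies end, and one item follows women after delivery. The close of Follow-up evaluations also says that treatment and follow-up will continue long term, and that women unwilling to have a hysterectomy will be watched closely. The legend of Fig. 2 marks halted protocol treatment, and the figure itself is not shown. Procedures after withdrawal are often left to a full protocol.

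Part of this stands. The absence of later data is an inference; no sentence says it. Stopping treatment and leaving the trial can also both apply, so the firmest conflict is between the mandatory and the advisory wording. But the closing remarks on long-term follow-up sit next to complete responders and speak of watching for recurrence, which presupposes remission. If they were meant to cover non-responders, they contradict the withdrawal rule and still need correction. The rule is stated in the article, so this is more than omitted detail.

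The reply is also right on consequences. Pregnancy attempts are described after remission, non-responders are advised to have surgery, and the device is a contraceptive. Scoring a non-responder as not pregnant would usually be correct.

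**Conclusion.** The point holds as a conflict between stated rules, with a likely but unquantified loss of later data. It should be fixed, but it does not undermine the main endpoint of a phase II trial that describes itself as not confirmatory. About 32 to 48 of 88 women (36% to 55%) would lack pCR at month 12 and leave under the literal rule.

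That range rests on three assumptions: 44 women per arm; planning rates quoted mostly for LNG-IUD alone and MA alone; and, at the upper end, 45% applied to both arms although it is the lower limit of the LNG-IUD estimate.

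A reader might infer more than the documents support:

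- That all 32 to 48 women certainly have no later data. This is not stated, and Efficacy assessments makes leaving advisory.
- That the 12-month pCR comparison is biased. It is not materially affected.
- That harm to non-responders goes unrecorded. Progression on biopsy is captured, and imaging is scheduled at months 6 and 12; the gap is what is found at later surgery, and adverse events after leaving.
- That the pregnancy comparison is seriously distorted. Only women who decline surgery are in real doubt, and their number is unknown.

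**What to change.** 1. Reconcile Criteria for discontinuation of trial treatment, Efficacy assessments (items C and E) and Follow-up evaluations so that each event has one stated consequence, including whether leaving is mandatory or advised. Which treatment rule applies is for the investigators; this review does not choose one.
2. State separately that leaving protocol treatment does not end data collection. Unless consent is withdrawn, record to month 24, by chart review or telephone: date of hysterectomy and final pathology (grade and stage), subsequent treatment, pregnancy and birth outcome, and adverse events.
3. Report pregnancy and live birth per randomised woman, by arm.

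The cost is protocol wording, a short form and some contact work at one centre. No biopsy, visit or participant is added. Some women treated elsewhere will still be lost, and their number should be reported by arm.

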### Data monitoring committee

The data monitoring committee (DMC) will be composed of clinical trial specialists, including a biostatistician, who are not associated with the study. The committee will meet at least twice a year, and all data obtained from the trial will be evaluated by the committee.

The DMC will review unblinded outcome data for safety and efficacy, and judge if there is evidence that either treatment is unsafe and the trial should be discontinued. The DMC will also advise the Trial Steering Committee of any evidence of unethical treatment or unacceptably serious adverse events.

The IBM Clinical Development Management System (IBM Corporation, Somers, New York), which is based on an EDC (Electronic Data Capture System), will be used to manage the data in this study.

### Sample size

According to a previous study, the mean pCR rate for LNG-IUD alone was 68% (95% confidence interval [CI]: 45–86%) [30], it was assumed that the rate in the MA-alone group will be 60%. Based on a prior study [38], we anticipate that the true pCR rate will be closer to the lower confidence limit of 45%. Patients who become pregnant during the trial will be withdrawn from the study and treated as non-recurrence in-trial cases.

The sample size was estimated by software G*Power version 3.1 (Heinrich-Heine-Universität Düsseldorf, Düsseldorf, German). The effect size, w, of the 2-group contingency table was set at a medium level of 0.3, type I error (alpha) at 0.05, 2-tailed, and power was set at 0.80, chi-square test. The size ratio between the 2 groups was set at 1:1. The estimated minimum required sample size of each group is 44, and the total sample size is 88.

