**Method and design:**

This will be an open-label, 2-armed, randomized, phase-II single-center trial of LNG-IUD plus metformin or megestrol acetate (MA) plus metformin. A total of 88 participants will be randomly assigned into 2 treatment arms in a 1:1 ratio. Clinical, laboratory, ultrasound and radiology data, will be collected at baseline, and then at 3, 6, 9, 12, 18, and 24 months. EC biomarkers will be collected at baseline. The primary aim is to determine the efficacy of a levonorgestrel-releasing intrauterine device (LNG-IUD) plus metformin, or megestrol acetate (MA) plus metformin in achieving pathological complete response (pCR) at 12 months, as well as post-treatment pregnancy outcomes and recurrence rate. The secondary aims are to predict the response to an LNG-IUD plus metformin and MA plus metformin via clinical, blood, and tissue predictive biomarkers.

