However, the outcomes of treatment with an LNG-IUD plus metformin, or MA plus metformin have not been compared. The primary aim of this phase II, 2-arm randomized trial is to determine the effectiveness of an LNG-IUD (Mirena®) plus metformin, and MA plus metformin to achieve a pathological complete response (pCR) at 12th months, pregnancy outcomes, and recurrence rates. The secondary aim is to predict the response to treatment with an LNG-IUD plus metformin, and MA plus metformin using clinical data and blood and tissue predictive biomarkers.

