Matsuo et al. reported that for patients with endometrial dysplasia, concurrent metformin administration was associated with an improved response in women using the LNG-IUD as compared with those receiving metformin plus progesterone (oral progesterone/LNG-IUD) treatment [43].

This proposed trial has strengths and weaknesses. A marked strength is that no high-quality studies are comparing the efficacy of an LNG-IUD plus metformin or MA plus metformin in the treatment of early EC. In other relevant studies, the primary endpoint is the pathological response rate while in the proposed trial the endpoints will be the pCR rate, pregnancy outcomes, and recurrence rates. The proposed trial is to investigate whether metformin combined with local progesterone and systemic progesterone have different therapeutic effects on endometrial lesions and whether there are different pathways for their “sensitization” effects. Finally, in ongoing trials (NCT01594879, NCT01943058, NCT02035787, NCT04792749, NCT02065687, NCT01968317, NCT01697566), metformin is administered in combination with progestin, and is discontinued after remission. In these trials, only an anticancer effect of metformin is expected as an outcome. Since most of the participants of this trial will be obese, they are likely to develop insulin resistance and abnormal glucose metabolism. Thus, this trial will also evaluate the expected improvements in the metabolic profile following the addition of metformin. Strengths of our work also include its prospective design, standardized treatment protocol, and long duration of follow-up.

A limitation of this trial is that the design is not that of a confirmatory trial. In addition, this trial will not use a placebo control group. However, evaluation of the remission and relapse rates, which are associated with the primary endpoint, will be performed by a pathological review board. The evaluation will be conducted under blind and independent conditions. Therefore, we believe that it will be possible to maintain objectivity and reduce potential bias.

We hope that the current study will increase the level of evidence on the effectiveness of an LNG-IUD in treating early EC and EHA. We hope that the LNG-IUD may be recognized as an effective alternative therapy for EC and EHA in obese women wishing for fertility preservation.

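### Coding women who become pregnant as non-recurrent can lower the recurrence rate but never raise it, and withdrawing them contradicts the planned pregnancy follow-up

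*Protocol article*

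**What the plan says.** The rule stands in the Sample size section of the protocol article: "Patients who become pregnant during the trial will be withdrawn from the study and treated as non-recurrence in-trial cases".

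Recurrence and pregnancy are both central to the trial. The abstract adds them to 12-month pCR in the primary aim: "as well as post-treatment pregnancy outcomes and recurrence rate". The Introduction repeats this ("to achieve a pathological complete response (pCR) at 12th months, pregnancy outcomes, and recurrence rates"), and the Discussion presents it as what sets the trial apart: "in the proposed trial the endpoints will be the pCR rate, pregnancy outcomes, and recurrence rates".

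The Efficacy assessments section treats endometrial cancer that appears after a complete response as a recurrence. The same section plans follow-up beyond conception: "Pregnancy assessment: outcomes of abortion, premature delivery, and full-term delivery will be recorded", and "Patients with a successful pregnancy and delivery who desire to retain reproductive function will undergo regular endometrial biopsies and imaging studies".

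The Statistical analysis section plans to report miscarriage, stillbirth, live birth and gestational age, and also "the proportion of patients that give birth to a child".

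**The concern.** Pregnancy is an expected event here. Entry requires a wish to preserve fertility, and a woman in confirmed remission who wants a child stops her progestin and monitors ovulation. A rule that settles her recurrence status at conception may therefore touch a sizeable share of responders.

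Two things are at stake.

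- **Recurrence.** A woman coded as a non-event stays in the denominator and can never enter the numerator, whatever a later biopsy shows. If conception is more frequent or earlier in one arm, that arm looks better on recurrence for this reason alone. The planned chi-square comparison of percentages does nothing to correct it.
- **Pregnancy outcomes.** Miscarriage, birth and gestational age all come after the point at which the woman is withdrawn. Sites are told both to withdraw her and to record what happens next.

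**Working it through.** **The plan's own figure.** The sample size uses w = 0.3, two-sided alpha 0.05, power 0.80 and a chi-square test. I take 1 degree of freedom, for a 2 × 2 table. The noncentrality is N × w² = 88 × 0.09 = 7.92, which gives power 0.8035. N = 87 gives 0.7991, so 88 is the smallest adequate total. The stated number reproduces and does not depend on the pregnancy rule.

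**A case that shows the mechanism.** Suppose a woman has negative biopsies at months 3 and 6, conceives at month 8, miscarries at month 10 and has biopsy-proven cancer at month 18. Under Efficacy assessments she is a recurrence. Under Sample size she is a non-recurrence.

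**Inputs for the size.** The documents give none of these, so all are assumptions:

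- r, recurrence risk in responders who do not become pregnant: 20% to 30%
- q, share of responders who become pregnant: 40% in one arm, 20% in the other
- k, recurrence risk in pregnant responders relative to r: 0 to 1

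I also read the rule as keeping pregnant women in the denominator, and I take responders as that denominator.

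**Formulas.**

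- Rate with full follow-up = (1 − q)r + qkr
- Rate under the rule = (1 − q)r
- Shift caused by the rule = −qkr, which is never positive
- Spurious arm difference = (0.40 − 0.20) × k × r

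**Results (40% arm versus 20% arm).**

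| r | k | Full follow-up | Under the rule | Spurious difference |
|---|---|---|---|---|
| 20% | 0 | 12% vs 16% | 12% vs 16% | 0 points |
| 20% | 0.5 | 16% vs 18% | 12% vs 16% | 2 points |
| 20% | 1 | 20% vs 20% | 12% vs 16% | 4 points |
| 30% | 0 | 18% vs 24% | 18% vs 24% | 0 points |
| 30% | 0.5 | 24% vs 27% | 18% vs 24% | 3 points |
| 30% | 1 | 30% vs 30% | 18% vs 24% | 6 points |

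For example, with r = 30% and k = 0.5, the 40% arm has 0.60 × 0.30 + 0.40 × 0.5 × 0.30 = 0.24 with full follow-up and 0.60 × 0.30 = 0.18 under the rule.

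The relative understatement within an arm is qk / (1 − q + qk). At k = 1 it is 20% (q = 20%) and 40% (q = 40%). At k = 0.5 it is 0.10/0.90 = 11% and 0.20/0.80 = 25%.

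**Scale.** The Sample size section mentions pCR rates from 45% to 68%. With 44 per arm, that is 44 × 0.45 = 19.8 to 44 × 0.68 = 29.9, or about 20 to 30 responders. One recurrence recoded as a non-event moves the arm's rate by 1/30 to 1/20, about 3 to 5 points.

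**The case against.** A reader might infer from the withdrawal that pregnancy outcomes cannot be observed and that live births will be missing by rule. The documents do not support that. Conception itself is what triggers the rule, so the proportion conceiving is known. Efficacy assessments says that pregnancy outcomes will be recorded, and Statistical analysis plans to report them. The Sample size section does not say whether withdrawal ends treatment, study visits or all data collection. Outcomes are lost only on the last reading, and the other sections speak against it. What stands is a contradiction. It is a real one, because Follow-up evaluations uses withdrawal as the alternative to further follow-up.

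It is also tempting to quote only the 4 to 6 point difference, or a 20% to 40% relative understatement. Those figures need pregnant women to carry the full recurrence risk (k = 1). Pregnancy is attempted only after two consecutive negative biopsies, and a recurrence found before conception is already counted. The rule therefore hides only the risk after conception within the study period, so k may well be below 1. An arm difference further requires that conception differs by arm, which is assumed.

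Nor does the text say outright that biopsies after pregnancy are discarded. That is an inference from a status fixed at pregnancy.

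Finally, the authors say the trial is not confirmatory, and a shift of 3 to 6 points is about one or two women per arm. That limits the consequence, but it does not justify assigning an outcome in advance to part of the primary aim.

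**Conclusion.** The point holds for recurrence as an analysis error and for pregnancy outcomes as an internal contradiction.

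The direction is certain once pregnant women are kept in the denominator as fixed non-events: the recurrence rate falls, or stays the same if none of them recurs. The size is not known. Under the stated assumptions the spurious arm difference runs from 0 to 6 points, and no value in that range can be preferred from the documents.

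The 12-month pCR comparison is little affected, because pregnancy attempts follow confirmed remission. The rule does not say how pCR is coded for a woman who conceives before month 12. The correction is needed before follow-up proceeds, because recurrence data not collected after conception may not be recoverable later.

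**What to change.** 1. Remove the fixed non-recurrence coding from the Sample size section.
2. Reconcile that section with Efficacy assessments and Statistical analysis. State that any stop of protocol treatment at pregnancy does not end data collection. Whether and when treatment stops is a clinical matter on which this point takes no position.
3. Record each pregnancy to its outcome, and let the biopsies already planned after pregnancy count towards recurrence.
4. Analyse recurrence as time from pCR to the first biopsy positive for recurrence as the protocol defines it. Censor at the last biopsy when none follows pregnancy.
5. Handle hysterectomy without recurrence explicitly, for example as a competing event. Follow-up evaluations recommends hysterectomy to responders who have completed childbearing, so it will occur.
6. Add a sensitivity analysis for informative censoring, for example by giving women censored at pregnancy a recurrence risk of 0, 0.5 and 1 times that of the other responders in their arm.

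The cost is a change of wording and a modest amount of extra analysis. Biopsies after delivery and long-term follow-up are already foreseen, but those biopsies are planned only for women who still want to keep their fertility. Some women will therefore contribute censored rather than complete recurrence data.
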